### **7.11. Treatment of Investigational Product Overdose**

Any signs or symptoms of overdosage will be treated symptomatically. No specific antidote is known.

### **7.12. Occupational Safety**

Investigational product is not expected to pose significant occupational safety risk to site staff under normal conditions of use and administration. A Material Safety Data Sheet (MSDS) describing occupational hazards and recommended handling precautions either will be provided to the investigator, where this is required by local laws, or is available upon request from GSK.

## **8. CONCOMITANT MEDICATIONS AND NON-DRUG THERAPIES**

### **8.1. Permitted Medications**

All concomitant medications taken during the study will be recorded in the CRF with indication, dose information, and dates of administration. During the planned Carotid endarterectomy (visit 5) drugs administered for anaesthesia will be recorded in the CRF with the total dose administered and the date of administration (visit 5 date).

Commencement or a change in a lipid lowering medication is not permitted during the study (V1 to V7) or during the 4 weeks prior to randomisation.

### **8.2. Prohibited Medications**

Treatment with corticosteroids, warfarin and/or digoxin is prohibited during the study. In addition, the following potent CYP3A4 inhibitors are prohibited:

| HIV Antivirals | Potent Macrolides | Azole Antifungals |
|-----------------------|--------------------------|--------------------------|
| Delaviridine          | Clarithromycin           | Fluconazole              |
| Indinavir             | Erythromycin             | Itraconazole             |
| Nelfinavir            | Troleandomycin           | Ketoconazole             |
| Ritonavir             |                          | Voriconazole             |
| Saquinavir            |                          |                          |
|                       |                          |                          |

## 9. PATIENT COMPLETION AND WITHDRAWAL

### 9.1. Patient Completion

All patients will be considered to have completed the study upon completion of all the assessments and procedures up to and including Visit 7.

Any patient who enters the study, (i.e. gives written informed consent) but does not, **for any reason** complete the study according to the definitions given above, will be considered a withdrawal, irrespective of whether they have received any study medication.

### 9.2. Patient Withdrawal

#### 9.2.1. Patient Withdrawal from Study

Each patient participating in the study will be assigned a unique CRF/patient number. Enrolment to the study will continue until 99 patients have been randomised into the study. Study medication given to withdrawn patients will **not** be reused.

Patients who terminate their participation in the study due to adverse experiences should be followed up as appropriate (see Section 10) in order to determine the final outcome.

Every effort should be made to follow up patients who withdraw or are withdrawn from the study prematurely. CRFs of **all** patients entered into the study must be completed. For patients who withdraw prior to randomisation (i.e. during the run-in period), complete the Study Continuation/Withdrawal page in the CRF.

For patients withdrawing after randomisation complete the Study Conclusion page and the Early Withdrawal (7) Visit. Reasons for withdrawal must be noted on the Study Conclusion page for all randomised patients who do not complete the study. At the patient's final visit, collect any unused study medication, and record the date of the last dose of study medication on the Study Conclusion page.

#### 9.2.2. Patient Withdrawal from Investigational Product

Every effort must be made by the Investigator to keep patients in the study. However, a patient may be discontinued prior to completion of the study for the following reasons:

- Adverse experience (see Section 10).
- Protocol Violation: including lack of compliance with visit scheduling, or treatment with prohibited concomitant medications.
- Patient lost to follow-up.
- The patient requests an early discontinuation (**not** due to an adverse experience).
- Termination of the study by GSK

- Other: Document reason in the CRF.

All adverse experiences leading to withdrawal of a patient must be fully documented and followed-up as appropriate (see Section 10). To ensure that all withdrawals due to adverse experiences are correctly identified, "adverse experience" should only be checked as the reason for withdrawal on the Study Conclusion page for those patients for whom an adverse experience was considered to be the direct cause of the patient withdrawing from the study. This is particularly important when adverse experiences are ongoing at the time of withdrawal, but the reason for withdrawal is not related to the adverse experiences.

### **9.3. Screen and Baseline Failures**

Data will not be collected on the database for screen and/or baseline failures i.e. patients who withdraw from the study following informed consent, but before receiving double-blind study medication.

## **10. ADVERSE EVENTS (AE) AND SERIOUS ADVERSE EVENTS (SAE)**

The investigator is responsible for the detection and documentation of events meeting the criteria and definition of an AE or SAE as provided in this protocol. During the study, when there is a safety evaluation, the investigator or site staff will be responsible for detecting AEs and SAEs, as detailed in this section of the protocol.

### **10.1. Definition of an AE**

Any untoward medical occurrence in a patient or clinical investigation subject, temporally associated with the use of a medicinal product, whether or not considered related to the medicinal product.

An AE can therefore be any unfavourable and unintended sign (including an abnormal laboratory finding), symptom, or disease (new or exacerbated) temporally associated with the use of a medicinal product. For marketed medicinal products, this also includes failure to produce expected benefits (i.e. lack of efficacy), abuse or misuse.

Examples of an AE **includes**:

- Significant or unexpected worsening or exacerbation of the condition/indication under study. See Section 10.3, "Lack of Efficacy", for additional information.
- Exacerbation of a chronic or intermittent pre-existing condition including either an increase in frequency and/or intensity of the condition.
- New conditions detected or diagnosed after investigational product administration even though it may have been present prior to the start of the study.
- Signs, symptoms, or the clinical sequelae of a suspected interaction.

- Signs, symptoms, or the clinical sequelae of a suspected overdose of either investigational product or a concurrent medication (overdose per se should not be reported as an AE/SAE).
- Significant failure of expected pharmacological or biological action. See Section 10.3, “Lack of Efficacy” for additional information.

Examples of an AE **does not include** a/an:

- Medical or surgical procedure (e.g., endoscopy, appendectomy); the condition that leads to the procedure is an AE.
- Situations where an untoward medical occurrence did not occur (social and/or convenience admission to a hospital).
- Anticipated day-to-day fluctuations of pre-existing disease(s) or condition(s) present or detected at the start of the study that do not worsen.
- The disease/disorder being studied, or expected progression, signs, or symptoms of the disease/disorder being studied, unless more severe than expected for the patient’s condition.

For GSK clinical studies, AEs may include pre- or post-treatment events that occur as a result of protocol-mandated procedures (i.e., invasive procedures, modification of patient’s previous therapeutic regimen). Planned carotid endarterectomy is not a protocol-mandated procedure.

## 10.2. Definition of a SAE

A serious adverse event is any untoward medical occurrence that, at any dose:

- a results in death.
- b is life-threatening.

*NOTE: The term 'life-threatening' in the definition of 'serious' refers to an event in which the patient was at risk of death at the time of the event. It does not refer to an event, which hypothetically might have caused death, if it were more severe.*

- c requires hospitalisation or prolongation of existing hospitalisation.

*NOTE: In general, hospitalisation signifies that the patient has been detained (usually involving at least an overnight stay) at the hospital or emergency ward for observation and/or treatment that would not have been appropriate in the physician’s office or out-patient setting. Complications that occur during hospitalisation are AEs. If a complication prolongs hospitalisation or fulfills any other serious criteria, the event is serious. When in doubt as to whether “hospitalisation” occurred or was necessary, the AE should be considered serious.*

*Hospitalisation for elective treatment of a pre-existing condition that did not worsen from baseline is not considered an AE.*

- d results in disability/incapacity, or

*NOTE: The term disability means a substantial disruption of a person's ability to conduct normal life functions. This definition is not intended to include experiences of relatively minor medical significance such as uncomplicated headache, nausea, vomiting, diarrhoea, influenza, and accidental trauma (e.g. sprained ankle) which may interfere or prevent everyday life functions but do not constitute a substantial disruption.*

- e is a congenital anomaly/birth defect.
- f Medical or scientific judgement should be exercised in deciding whether reporting is appropriate in other situations, such as important medical events that may not be immediately life-threatening or result in death or hospitalisation but may jeopardize the patient or may require medical or surgical intervention to prevent one of the other outcomes listed in the above definition. These should also be considered serious. Examples of such events are invasive or malignant cancers, intensive treatment in an emergency room or at home for allergic bronchospasm, blood dyscrasias or convulsions that do not result in hospitalisation, or development of drug dependency or drug abuse.

#### **10.2.1. Surgery-Related Events or Outcomes Not Qualifying as SAEs**

Carotid endarterectomy is associated with significant morbidity/mortality (risk of stroke, bleeding, death). Such post-operative events will not be recorded as SAEs.

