### **2.2. Secondary**

- To determine the change in Lp-PLA2 activity in blood after treatment with SB-480848
- To determine the change in Lp-PLA2 mass in blood after treatment with SB-480848
- Lp-PLA2 mass in plaque after treatment with SB-480848, compared with placebo
- To evaluate the dose response effects of SB-480848 on plasma and plaque Lp-PLA2 levels
- Levels of defined biomarkers in plaque after treatment with SB-480848, compared with placebo
- To determine the change in levels of defined biomarkers in blood after treatment with SB-480848
- To investigate the correlation between biomarkers and Lp-PLA2 in blood and plaque after treatment with SB-480848
- To characterise the pharmacokinetics (PK) of repeat oral doses of SB-480848 and its metabolite (SB-553253) in this patient population
- To investigate the pharmacodynamics (PD) of SB-480848 following repeat oral administration to this population
- To further investigate the safety and tolerability of SB-480848 through observations of adverse experiences, vital signs, laboratory tests, and effects on 12-lead ECG.
- To determine a change in the oxidised lipids and their metabolites including lyso-PC levels in plasma and in carotid plaques after 14(+/-) days treatment with SB-480848 compared to placebo.

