### **10.5. Time Period, Frequency, and Method of Detecting AEs and SAEs**

Any pre-existing conditions or signs and/or symptoms present in a patient prior to the start of the study (i.e. before informed consent) should be recorded in the Medical/Surgical History section within the CRF.

In order to fulfil international reporting obligations, SAEs that are related to study participation (e.g. procedures, invasive tests, change from existing therapy) or are related to a concomitant medication will be collected and recorded from the time the patient consents to participate in the study until he/she is withdrawn or completes.

Any medical occurrences which occur after informed consent is obtained but prior to starting active or randomised treatment will be documented on the Baseline Signs & Symptoms section within the CRF.

All AEs occurring after administration of the first dose of study medication and on or before the final visit must be reported on the Adverse Event form in the CRF. All AEs must be recorded irrespective of whether they are considered drug related.

At each visit/assessment in the period defined above, AEs will be evaluated by the investigator and recorded in the appropriate AE/Serious AE section of the CRF.

Any AEs already documented at a previous assessment and designated as ongoing, should be reviewed at subsequent visits as necessary. If these have resolved, the documentation in the CRF should be completed. If an AE changes in intensity/frequency then this should be recorded as a separate event (i.e. a new record started).

As a consistent method of soliciting AEs, the patient should be asked a non-leading question such as:

"Have you felt different in any way since starting the new treatment/or since the last visit?"

or

"How do you feel?"

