| Chest X-ray (if one not available within previous 6 months) | ✓                  |                         |          |                                                 |                                   |                         |                                    |
| Fasting blood draw for HbA1c, insulin                       |                    | ✓                       |          |                                                 |                                   |                         |                                    |
| Blood sampling for haematology, clinical chemistry          | ✓                  | ✓                       | ✓        |                                                 | ✓                                 |                         | ✓                                  |
| Blood sampling for peripheral lymphocytes                   |                    | ✓                       |          |                                                 |                                   |                         | ✓                                  |
| 12-lead ECG                                                 |                    | ✓           |          |                                                 | ✓                     |                         |                                    |
| Concomitant medication                                      | ✓                  | ✓                       | ✓        |                                                 | ✓                                 |                         | ✓                                  |
| Physical examination, vital signs                           | ✓                  | ✓                       | ✓        |                                                 | ✓                                 |                         | ✓                                  |
| Baseline signs and symptoms/Adverse events                  | ✓                  | ✓                       | ✓        |                                                 | ✓                                 |                         | ✓                                  |

Continued

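### Section 10.2.1 removes post-operative stroke, bleeding and death from SAE status, against Section 10.2 and with drug still on board; they remain only as AEs without a seriousness flag

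*Protocol*

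**What the plan says.** Protocol Section 10.2.1 opens with the risk of the operation: "Carotid endarterectomy is associated with significant morbidity/mortality (risk of stroke, bleeding, death"). It then rules: "Such post-operative events will not be recorded as SAEs". The section has no other content. It sets no end to the post-operative period and does not say what happens if the investigator suspects the study drug or finds the event worse than expected.

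Section 10.2 gives the general definition: "A serious adverse event is any untoward medical occurrence that, at any dose", followed by a list of criteria whose first item reads "a results in death". Life-threatening events are also listed. On complications during a hospital stay, the same section says: "If a complication prolongs hospitalisation or fulfills any other serious criteria, the event is serious".

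Section 10.5 sets the collection window: "All AEs occurring after administration of the first dose of study medication and on or before the final visit must be reported". That window contains the operation and the recovery period up to Visit 7. Section 11.8.2 plans by-arm summaries of all AEs, treatment-related AEs, AEs leading to withdrawal from study medication, and SAEs, together with a full AE listing. Safety is a secondary objective in Section 2.2: "To further investigate the safety and tolerability of SB-480848 through observations of adverse experiences".

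**The concern.** The two sections give opposite instructions for the same patient. A fatal stroke on the day after surgery is an SAE under Section 10.2 and may not be recorded as one under Section 10.2.1.

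The conflict would matter less if exposure had ended well before surgery, but the design does the reverse. Dosing runs up to the day before the operation because the primary endpoint is enzyme activity in the excised plaque. A post-operative event therefore happens under drug.

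Several safeguards depend on SAE status: reporting to the sponsor within 24 hours, the sponsor's option to unblind a reported case, the expedited report to investigators, and the by-arm SAE summary. If Section 10.2.1 is followed as written, deaths, strokes and bleeds after surgery reach none of these.

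**Working it through.** The protocol states no figure that could be reproduced here. The check has three parts.

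**1. Is drug present when these events occur?**

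Inputs: last dose on the day before surgery (Section 6.3.1.1); half-life 25-45 hours (Section 1.1); Visit 7 at 14 days after the last dose (Section 6). Under simple first-order decay, the fraction remaining is 2^(-t / half-life).

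| Time after last dose | Half-life 25 h | Half-life 45 h |
|---|---|---|
| 24 h | 2^(-24/25) = 0.51 | 2^(-24/45) = 0.69 |
| 48 h | 2^(-48/25) = 0.26 | 2^(-48/45) = 0.48 |
| 14 days (336 h) | below 0.001 | 2^(-336/45) = 0.006 |

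Five half-lives take 5 × 25 / 24 = 5.2 days to 5 × 45 / 24 = 9.4 days. Drug is present at surgery and through the early post-operative days, and is essentially gone by Visit 7. Section 7.3 points the same way: 24 hours after a dose at steady state it expects plasma enzyme inhibition of 85-90% at 80 mg and 60-65% at 40 mg.

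**2. What does Section 10.2.1 take away, and what does it leave?**

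| Item | Section | Post-operative stroke, bleeding, death |
|---|---|---|
| AE record, whatever the cause | 10.2, 10.5 | kept |
| Intensity grade and causality assessment | 10.7.1, 10.7.2 | kept |
| Ongoing review of AE data | 11.8 | kept |
| All-AE table by arm and AE listing | 11.8.2 | kept |
| Seriousness flag | 10.2 against 10.2.1 | lost |
| SAE summary by arm | 11.8.2 | lost |
| Report to sponsor within 24 hours | 10.9 | lost |
| Sponsor unblinding after a reported SAE | 7.4 | lost |
| Expedited Investigator Safety Report | 10.10 | lost |

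The summary of AEs leading to withdrawal from study medication is unlikely to pick these events up, because dosing has ended before surgery. Section 11.8.2 lists no separate table of deaths; the statistical analysis plan, which is not at hand, may add one. There is also an anomaly with Section 10.11. A death learned of after the patient has left the study and judged reasonably related to drug must be notified promptly, whereas a related death a few days after surgery, inside the study, has no SAE route.

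**3. How many events?**

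The protocol gives no event rate. At an assumed 2% to 6% risk of post-operative stroke, major bleeding or death:

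- in all 99 patients: 99 × 0.02 = 2.0 to 99 × 0.06 = 5.9 events
- per arm of 33: 33 × 0.02 = 0.7 to 33 × 0.06 = 2.0 events

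These would lose SAE status but would not be lost from the AE data.

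**The case against.** The strongest reply is that Section 10.2.1 is a deliberate, narrow exception. Its heading concerns surgery-related events, and Section 10.1 says the endarterectomy is not mandated by the protocol. The section removes a label, while recording, grading, causality assessment and tabulation all continue. Section 10.8 also gives the sponsor any post-mortem findings. Much of this stands, and it limits the point. Whether the exception was meant to cover an event that the investigator attributes to drug is unclear, but the text does not exclude such an event. None of the remaining safeguards replaces prompt reporting of a death.

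A reader might infer three stronger things, and the documents support none of them.

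- **That the safety tables omit these events.** Section 10.2 keeps in-hospital complications as AEs, Section 10.5 requires every AE up to the final visit to be recorded, and Section 11.8.2 tabulates all AEs by arm. Only the SAE summary lacks them.
- **That the safety objective cannot be met.** Section 2.2 pursues it through adverse experiences, vital signs, laboratory tests and ECG. It does not rest on the SAE label.
- **That events on the day after surgery go uncollected.** In Appendix 1 the row "Baseline signs and symptoms/Adverse events" has no tick at Visit 6. But Section 10.5 requires AE evaluation at every visit in the window, and Visits 5 and 7 are ticked. This is a table inconsistency.

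Two further limits apply. The decay figures show that drug is present, not that it affects these outcomes. And at 0.7 to 2 events per arm, no table in this trial could establish a difference between arms.

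**Conclusion.** The point holds in this form: Section 10.2.1 contradicts Section 10.2 on post-operative stroke, bleeding and death, without limit of cause, severity or time, in a period when 51-69% (24 hours) and 26-48% (48 hours) of the drug level remains. The consequence is an incomplete by-arm SAE summary and no prompt reporting of such events, including deaths. The events themselves stay in the AE data by arm, without a seriousness flag.

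The contradiction rests on the protocol text alone. The decay figures assume first-order elimination at the stated half-life and about 24 hours between last dose and surgery. The count of 2 to 6 affected patients rests wholly on an assumed 2-6% rate and on all 99 patients reaching surgery. The conclusion does not depend on that count: a single post-operative death would expose the conflict.

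**What to change.** Amend Section 10.2.1 to agree with Section 10.2: any post-operative event that meets the Section 10.2 definition is recorded as an SAE and appears in the SAE summary by arm. If the sponsor wants to limit the reporting load from anticipated surgical complications, it can list them in advance and confine the exemption to onward expedited reporting, leaving CRF recording and the report to the sponsor intact.

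As a minor consistency edit, tick the adverse-event row at Visit 6 in Appendix 1 so that it matches Section 10.5.

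The cost is amendment text and a few more SAE forms. No visit or procedure is added: the patient already has a visit on the day after surgery, with blood sampling.
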